Stationary cycling interventions for children with CP warrant further examination as they have the potential to improve strength and cardiorespiratory fitness with minimal requirements for balance and motor control. The purpose of this study is to evaluate the effectiveness of a stationary cycling intervention for children with spastic diplegic CP using a RCT design. We hypothesize that those children randomized to the cycling group will demonstrate a significant improvement in muscle strength, walking endurance, gross motor function and health related quality of life compared to those randomized to the control (no-cycling) group.

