### Sample size

Sixty subjects (30 cycling intervention, 30 no cycling control) will be recruited for this study. A sample size of 30 in each group will have 80% power to detect a moderate effect size of 0.7 (as well as a minimal clinically important difference) using a two group t-test with a 0.05 two-sided significance level. Power analyses were performed using joint moment data outcomes following an isokinetic strengthening intervention for children with CP [16]. A 10% subject attrition rate was factored into the analyses.

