#### Outcome data measurements

Outcome measures for this study include assessments at the body function and structure, activity and participation levels of the ICF. Primary outcome measures are: 1) knee joint extensor and flexor torque; 2) the Gross Motor Function Measure (GMFM) Sections D: Standing and E: Walking, Running and Jumping [38]; 3) the 600 Yard Walk-Run test [39] and 4) the Thirty-Second Walk test (30 sec WT) [40]. Secondary measures are: 1) the Pediatric Outcomes Data Collection Instrument (PODCI) [41], 2) the Pediatric Quality of Life Inventory™ (PedsQL) [42-44] and 3) instrumented gait analysis.

Knee joint extensor and flexor moments, commonly referred to as joint torque in a clinical setting, are measures at the body function and structure level of the ICF. A Kin-Com dynamometer (Chattanooga Group Inc., Hixson, TN) will be used for data collection at the Los Angeles site and a Biodex Multijoint System (Biodex Medical Systems Inc., Shirley, NY) at the Missouri site. The subject will be seated with the trunk slightly reclined. Straps at the waist, chest, thigh and distal aspect of lower leg will be used to secure the subject to the testing device. The axis of the device's moving arm will be aligned with the subject's knee joint center. The subject will be directed to observe the computer screen for visual feedback while being verbally encouraged by the investigator to provide maximum effort. Five repetitions of knee joint extension and flexion at 0, 30, 60 and 120 degrees/second will be performed bilaterally. The peak joint moment for each group of five contractions will be determined.

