The GMFM assesses performance at the activity level of the ICF. It has been shown to be valid [45] and reliable [46] for assessing children with CP. Two of the five dimensions, Dimension D: Standing (13 items) and Dimension E: Walking, running, and jumping (24 items) will be tested. GMFM sessions will be videotaped to permit review should a question about a particular score arise. Subjects will wear shorts and be tested barefoot and without assistive devices or ankle-foot orthoses. The evaluation therapists will follow the procedures outlined in the Gross Motor Function Measure User's Manual [38] for testing and scoring. Each item will be scored as 0 = does not initiate, 1 = initiates, 2 = partially completes, 3 = completes or NT = not tested. The data will be analyzed using the GMFM-66 Ability Estimator Software. The advantage of the software is the conversion of the ordinal data into an interval scale. This will allow for a more accurate estimate of the child's ability and provide a measure that is equally responsive to change across the spectrum of ability levels [38].

The 600 yard walk-run test [39] assesses walking and/or running endurance at the activity level of the ICF. This test is an indirect measure of cardiorespiratory fitness and is reflective of a child's ability to participate in play and sport activities. It is a standardized physical fitness test developed for school-age children. Fernhall et al. [39] used this test for children with intellectual disabilities and found a high correlation with laboratory measures of peak V0_2_. During this test, children are asked to complete a 600 yard distance as fast as possible by running, walking or a combination of both. The distance required will be clearly explained so they may pace themselves. Orange cones will be placed to visibly mark the perimeter of the circular path. Subjects will be encouraged verbally to continue walking or running until they complete the 600 yard distance. If a subject cannot complete this distance within 15 minutes or stops for more than five seconds, the test will be stopped. At the end of the test, the distance completed and the time will be recorded. Distances of less than 600 yards will be measured using a distance-measuring wheel. Outcomes include the distance the child is able to complete, the time for completion and the speed.

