The 30 sec WT assesses walking function at the activity level of the ICF and is reflective of a child's ability to walk within the school environment. Normative data for 227 children between the ages of six and 13 years are available for comparison [40]. This test will be administered in a gymnasium by asking the subject to walk at a comfortable speed and to stop when 30 seconds have elapsed. Children will be instructed to walk as if they were the leader in a line at school. The examiner will monitor time using a stopwatch. When 30 seconds have elapsed, the examiner will instruct the subject to "freeze" and not move until his or her foot position is marked. The distance from the starting line to the heel of the forward-most foot will be measured using a distance-measuring wheel. Outcomes will be the total distance walked and walking speed.

The health-related quality of life questionnaires to be used for this study assess multiple domains of function within the ICF but focus on environmental and personal contextual factors. Questionnaires will be administered in an interview format. The PODCI Scale was developed to assess health-related quality of life in children from 7 – 19 years of age. It demonstrated good reliability, construct validity and sensitivity to change over a 9-month period [41]. This questionnaire will be completed by the parent, or guardian, and all adolescents (11–18 years). Individuals will be asked to respond to questions by choosing from a list of possible answers. A Spanish language version of this tool will be available. Interpreters will be made available for other languages. There are eight scales: upper extremity and physical function, transfer and basic mobility, sports/physical functioning, pain/comfort, treatment expectations, happiness, satisfaction with symptoms and a global functioning scale (a combined scale calculated from the first four scales). All components are transformed to a 0–100 scale for analyses.

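### Four primary measures of equal standing have no lead measure, testing order or success rule, while the trial is sized for one test at 0.05

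*Protocol article*

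**What the plan says.** Under Outcome data measurements the article lists the primary measures in one run: "Primary outcome measures are: 1) knee joint extensor and flexor torque; 2) the Gross Motor Function Measure (GMFM) Sections D: Standing and E: Walking, Running"; the list ends with "3) the 600 Yard Walk-Run test [39] and 4) the Thirty-Second Walk test (30 sec WT"). None is ranked above another.

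The same section then describes what each measure yields:

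- Torque: "Five repetitions of knee joint extension and flexion at 0, 30, 60 and 120 degrees/second will be performed bilaterally", with one peak moment taken from each set of five.
- GMFM: Dimensions D and E, analysed through the GMFM-66 software.
- 600 Yard Walk-Run: "Outcomes include the distance the child is able to complete, the time for completion and the speed".
- 30 sec WT: "Outcomes will be the total distance walked and walking speed".

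The Sample size section bases power on joint moment data from an isokinetic strengthening study, "using a two group t-test with a 0.05 two-sided significance level". It does not say which joint, direction, speed or limb was used. This is the only significance level in the article.

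Data analyses applies t-tests or Wilcoxon tests to change from baseline, within and between groups, for primary hypotheses in the plural. It adds analysis of covariance for the primary measures. It gives no level, order or success rule. The Background hypothesis is that cycling children "will demonstrate a significant improvement in muscle strength, walking endurance, gross motor function and health related quality of life".

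**The concern.** With four equal primaries and no rule for combining them, a significant result on any one could be reported as a positive primary finding. The 5% error rate implied by the sample size calculation belongs to one pre-named test, not to the best of four. The latitude grows if the variables within a measure can also be chosen after the data are seen: one torque speed or direction among several, or time rather than distance in the walk-run.

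The sample size makes no allowance for several tests. An adjustment added later would therefore come out of power that was planned for a single comparison.

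**Working it through.** **Inputs.** From the article: four primary measures; two-sided 0.05; 30 per group; standardized effect d = 0.7; 10% attrition, so 30 × 0.9 = 27 evaluable per group; stated power 80%. Correlations between outcomes are not given, so they are assumed and shown as a range.

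**1. The plan's own figure.** Power of the two-group t-test comes from the noncentral t distribution with 2n − 2 degrees of freedom and noncentrality d × √(n/2).

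- n = 30: 0.7 × √15 = 2.71, power 76.0% (77.4% by normal approximation).
- n = 27: 0.7 × √13.5 = 2.57, power 71.4% (73.0% by normal approximation).

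The stated 80% is not reproduced. With 30 per group, 80% power corresponds to d = 0.736, which rounds to 0.7; with 27 it corresponds to d = 0.777. That is a separate matter. Here 71.4% serves as the baseline for step 4.

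**2. Four measures, each tested at 0.05.** Under independence the chance of at least one false positive is 1 − 0.95⁴ = 1 − 0.8145 = 18.5%. For correlated tests, multivariate normal statistics with equal correlation r were simulated (400,000 draws), counting draws with any |Z| above the two-sided 0.05 limit:

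| r | 0.3 | 0.5 | 0.7 | 0.8 | 0.9 |
|---|---|---|---|---|---|
| chance | 17.4% | 15.5% | 13.0% | 11.4% | 9.4% |

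**3. If every listed variable were also tested.** Torque gives 2 directions × 4 speeds × 2 limbs = 16; GMFM-66 gives 1; the walk-run gives 3; the 30-second test gives 2. The total is 16 + 1 + 3 + 2 = 22. Only 21 are distinct, because 30-second speed is distance divided by 30.

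Under independence: 1 − 0.95²² = 67.6% (1 − 0.95²¹ = 65.9%). With 22 equally correlated variables:

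| r | 0.3 | 0.5 | 0.7 | 0.8 | 0.9 |
|---|---|---|---|---|---|
| chance | 56.9% | 43.9% | 30.1% | 23.2% | 15.9% |

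A structured pattern gives 25% to 47%. It assumes torque values correlated 0.5 to 0.9 with each other, walk-run outcomes 0.9, the two 30-second outcomes almost 1, and different measures 0.2 to 0.5. For jointly normal two-sided tests, independence is the worst case, so 68% is a ceiling and not an estimate.

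**4. Cost of an equal split.** Bonferroni over four uses 0.05 / 4 = 0.0125. At d = 0.7 this gives power of 49.9% with 27 per group, against 71.4% at 0.05, a loss of about 21 points. With 30 per group it gives 55.6%. Restoring 80% would need 48 evaluable per group, or 48 / 0.9 = 53.3, rounded up to 54 recruited.

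**The case against.** The strongest reply is that the article says what is measured, not how many tests decide the trial. A reader might infer 22 primary tests, each at 0.05, and a false positive chance near two in three. The document does not support that:

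- The 16 torque peaks come from a measurement procedure, and nothing says that each is a separate primary test. Combining limbs and speeds is commonly left to an analysis plan that is not shown.
- The level 0.05 appears only in the sample size statement, so testing each measure at 0.05 is an inference.
- The two 30-second outcomes are one number on two scales. For children who finish 600 yards, distance is constant and speed is 600 divided by time.

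This part of the reply stands, and it limits the firm claim to the four named measures.

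Three other tempting readings also fail. Nothing says that left and right limbs will be analysed as separate observations, so double-counting of children is not established. The quality of life item in the Background hypothesis is loose wording, since the article plainly classes those instruments as secondary. And the power statement concerns a standardized effect, so it applies to any single outcome with that effect, not to torque alone.

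It can also be said that a Phase I label and sparse prior research weaken the case for strict error control, and that an unseen analysis plan may adjust for multiplicity. But the article describes an efficacy evaluation with a formal power claim. The choice of four equal primaries against a sample size for one test is made in the article itself, and a later adjustment would draw on power already committed.

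Reading the Background's joined list as requiring success on every item would remove the inflation. No such rule is stated, and that list includes a secondary outcome.

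**Conclusion.** The point holds for the four named measures. If each is tested at 0.05, the chance of at least one false positive primary result is 18.5% under independence and about 9% to 17% at correlations of 0.9 to 0.3, against 5% for one pre-named test. It rises to roughly 16% to 57% over the same correlations only if all the variables listed within measures are tested separately as well, which the article leaves open but does not state.

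These figures rest on two assumptions: that 0.05 applies to each test, and the correlations chosen. Within-group contrasts and the analysis of covariance, which is not ranked against the t-test, are further routes to a positive result and are not counted. The matter should be corrected; it does not invalidate the design.

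**What to change.** Before any unblinded analysis, amend Outcome measures and Data analyses as follows.

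1. Name one analysis variable per primary measure. For torque, use one summary per child combining the two limbs, with direction and speed stated. For GMFM, use the GMFM-66 score. For the walk-run, choose one of distance, time or speed; distance is at its ceiling for finishers and completion time does not exist for children who are stopped, so the choice matters. For the 30-second test, use distance only.
2. Designate one lead variable, tested at two-sided 0.05. The torque summary matching the data behind the sample size is one candidate. The sponsor must name it, because the article does not identify that variable, and should weigh that the two sites use different dynamometers.
3. If the lead test succeeds, test the other three in a pre-stated fixed order, or by Holm among the three.
4. Class all remaining variables as secondary, and state that quality of life in the Background hypothesis is a secondary aim.

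This costs wording only: no extra children, visits or measurements. The real price is that a later measure is confirmatory only if the earlier step is passed. The alternative of an equal Bonferroni split would cut power per measure from 71% to 50% at 27 per group and d = 0.7, which is why an ordered scheme is preferable.

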### Physical activity calendars

All subjects will be provided with calendars and stickers at their initial baseline evaluation to chart their daily physical activity levels throughout the 12-week intervention period. These data are a measure at the ICF level of participation and will inform the investigators of periods of illness or injury that could affect data interpretation. Activities will be classified into four different levels: high, moderate, low and bedrest. The subject will be instructed to place a sticker on each day of the calendar that corresponds to their participation in the following activity levels. A high activity level is defined as participating in activities such as running/jogging, contact sports, hiking, dancing, climbing stairs or biking for over a one-hour period. A moderate activity level is defined as participating in the above activities over a 30-minute period or activities such as swimming, skateboarding, scooter riding or walking for approximately one-hour. A low activity level indicates a sedentary day with activities such as schoolwork, television or computer games. Bedrest indicates that a child is inactive for the entire day due to illness or injury. A folder will be given to the family with calendars, written instructions, colored stickers and contact information for the investigators. Materials are available in English and Spanish. Subjects randomized to the cycling intervention group will be instructed to exclude the cycling intervention when recording their daily activity levels. They will begin calendar recording following their baseline data collection and will return them at the follow-up evaluation session.

### Data analyses

Student t-tests (if normally distributed) or Wilcoxon rank sum tests (if non-normal) will be used to contrast the change from baseline within and between the intervention and control groups for the primary hypotheses. Analysis of covariance procedures will be used to contrast changes adjusting for selective voluntary motor control (good versus fair) and age group (younger, 7–11 years) and (older, 12 – 18 years) for primary outcome measures.

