The Institutional Review Boards of the University of Southern California, University of California at Los Angeles, Missouri State University, the State of California, Orthopaedic Hospital in Los Angeles, California and CoxHealth Hospital in Springfield, Missouri granted approvals for this research protocol. This study has a pre-post, control group design with single-blinding. Subjects will be randomly assigned to intervention versus control groups. There are two stratifying variables; age (younger, 7–11 and older, 12–18 years) and selective voluntary motor control ability (good versus fair). Randomization to the intervention or control group will be blocked by these two variables. The assessment of selective motor control ability for children with CP has been described by Staudt and Peacock [33]. Good selective motor control is defined as the ability to isolate knee and ankle movement out of synergy (knee extension with the hip in flexion and ankle dorsiflexion with the knee in extension). Fair selective motor control is defined as the ability to isolate knee movement without obligatory hip movement. Only subjects who demonstrate good selective motor control bilaterally will be placed in the good selective motor control category for stratification. Subjects who have poor selective motor control (cannot isolate knee and ankle joint motion out of synergy) bilaterally will be excluded from the study. All others will be placed in the fair selective motor control category.

Interventions will be performed by physical therapists in community clinics throughout Southern California and Southwest Missouri. Evaluations will take place at the University of Southern California or Missouri State University and will be performed by physical therapists blinded to subject group randomization. Evaluation and intervention physical therapists will attend instructional sessions and receive a written manual of procedures specific to either evaluation or intervention protocols. Performance will be videotaped during mock sessions and scored by members of a standards committee using a checklist of critical components for each protocol. To participate in the study, therapists must achieve a minimum score of 90% accuracy. In addition, they will be provided with feedback for aspects of the protocol that are not performed optimally.

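### Within-group change tests are listed for the primary hypotheses although the hypothesis is comparative, and the rank-sum test named does not fit a paired within-group contrast

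*Protocol article*

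**What the plan says.** The Data analyses section gives one pair of tests for two kinds of contrast: "Student t-tests (if normally distributed) or Wilcoxon rank sum tests (if non-normal) will be used to contrast the change from baseline within and between" the two groups. Both kinds are assigned to the primary hypotheses ("to contrast the change from baseline within and between the intervention and control groups for the primary hypotheses"). Neither is ranked above the other, and within-group change is not called descriptive. No paired t-test or signed-rank test is named. The section then adds an adjusted comparison for the primary outcomes: "Analysis of covariance procedures will be used to contrast changes adjusting for selective voluntary motor control" and age group.

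The Background states the hypothesis as improvement in strength, walking endurance, gross motor function and quality of life "compared to those randomized to the control (no-cycling) group". The Methods/design section says "This study has a pre-post, control group design with single-blinding", so each child has a baseline and a follow-up value. The Sample size section plans 30 per group, with 10% attrition, for a two-group t-test at the two-sided 0.05 level. It powers no within-group test.

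**The concern.** There are two separate faults, with opposite consequences.

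**Within-group tests attached to a comparative hypothesis.** A within-arm test asks whether children in that arm changed. It does not ask whether they changed more than controls. Participants are 7 to 18 years old and repeat effort- and skill-dependent tests about three months apart, so some improvement from growth or practice is plausible in both arms. A within-cycling test counts that shared improvement. If such a result is reported under the primary hypotheses, it carries no 5% error rate for the claim that cycling works.

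**The non-parametric test named.** If data are non-normal, the stated choice is "Wilcoxon rank sum tests (if non-normal"). This test compares two independent samples. It is sound for comparing change scores between arms. It does not fit baseline and follow-up values from the same children, nor a single sample of change scores from one arm.

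**Working it through.** **Inputs from the article.** 30 per group; 10% attrition, so 30 × 0.9 = 27 completers per group; two-sided 0.05; standardised effect 0.7; stated power 80%.

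**Inputs assumed, because the article does not give them.** The change shared by both arms, taken as 0.2 to 0.7 SD of change. The baseline to follow-up correlation, taken as 0.5, 0.7 and 0.9.

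**The article's own figure.** Exact two-sided t power at effect 0.7 is 76.0% with 30 per group and 71.4% with 27, so the stated 80% is not reproduced. That is a separate matter and does not affect this point. What matters here is that the powered test is the between-group one.

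**Step 1: within-cycling test when cycling has no effect.** Let both arms change by d (in SD of change). The within-arm paired t-test has noncentrality d√n. Its rejection rate is p = P(|T| > t₀.₉₇₅,ₙ₋₁), where T is noncentral t with n − 1 degrees of freedom. For n = 27 the critical value is 2.056. The arms are independent, so the pattern of cycling significant and control not significant has probability p(1 − p). The between-group test rejects at 5%, because the difference in mean change is zero.

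| d | d√27 | Within-cycling significant (p) | Cycling significant, control not: p(1 − p) | Between-group test |
|---|---|---|---|---|
| 0.2 | 1.04 | 17% | 14% | 5% |
| 0.3 | 1.56 | 32% | 22% | 5% |
| 0.4 | 2.08 | 52% | 25% | 5% |
| 0.5 | 2.60 | 71% | 21% | 5% |
| 0.7 | 3.64 | 94% | 6% | 5% |

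At d = 0.4, for example, p = 0.517 and 0.517 × 0.483 = 0.250. With 30 per arm, p is 18% to 19% at d = 0.2 and 96% at d = 0.7, so attrition does not drive the result.

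**Step 2: rank-sum on paired data.** This step supposes that rank-sum is applied to baseline versus follow-up values in one arm. Data were simulated as bivariate normal pairs, n = 27, with a true change of 0.3 baseline SD.

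| Assumed correlation | Rank-sum, no change | Rank-sum power | Signed-rank power |
|---|---|---|---|
| 0.5 | under 1% | about 11% | about 30% |
| 0.7 | about 0.1% | about 7% | about 47% |
| 0.9 | about 0% | 2–3% | 90–92% |

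With no change, signed-rank rejects in about 5% of runs, as it should. Rank-sum ignores the pairing. With positively correlated pairs it rejects too rarely and loses power, and the loss grows with the correlation.

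**The case against.** The strongest reply is that the article already fixes the comparison that matters. The hypothesis is comparative, the powered test has two groups, the between-group contrast is named, and an ANCOVA adjusted for both stratifiers is planned. Nothing says that a within-arm result alone, or significance in one arm and not the other, will count as success. This stands. A reader might infer from Step 1 that the trial has a false-positive rate of up to 94%, or that the controlled comparison is missing. The article supports neither. The percentages show what a within-arm test would do if it were read as evidence for cycling.

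A second reply is that this is shorthand in a two-sentence analysis section: Student t-tests can cover both paired and two-sample forms, and the Wilcoxon label was stretched in the same way. The text also speaks of change from baseline, so it does not clearly call for rank-sum on raw baseline and follow-up values. This stands in part. Step 2 is therefore conditional. But the name given is that of the independent-samples test, and no reading makes it right for one arm's change scores.

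A third tempting inference is that the rank-sum error lets growth or practice pass as a cycling effect. It does the opposite: it would hide change. The risk of misreading comes only from the within-group tests.

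Regression to the mean might also be cited as a source of shared change. The inclusion and exclusion criteria do not select children on extreme values of a primary outcome, so that argument is not relied on here.

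**Conclusion.** The point holds at moderate severity. As written, the plan places within-group tests beside the between-group test under the primary hypotheses and does not say which decides. A within-arm test does not address the stated hypothesis. With no cycling effect and an assumed shared change of 0.2 to 0.7 SD, it would be significant in 17% to 94% of trials, against 5% for the between-group test. The exact percentages rest on that assumed range and on 27 completers per arm; the direction does not, since any shared change raises the within-arm rate above 5% and leaves the between-group rate alone.

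The rank-sum problem is smaller and distinct. The test named is suitable between groups and misnamed within groups. If it were used on paired values, the cost would be lost power: substantial at a correlation of 0.5 and nearly complete at 0.9. The point is not more severe, because a valid unadjusted comparison and an adjusted one are both already in the plan.

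**What to change.** Replace the wording with a statement of three things:

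1. Only the between-group contrast of change from baseline (or the planned ANCOVA, if that is preferred) tests the primary hypotheses.
2. Within-group changes are descriptive and reported with confidence intervals.
3. Any within-group test that is kept is a paired t-test or a Wilcoxon signed-rank test, and rank-sum is reserved for comparing change scores between groups.

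This costs a sentence or two. It needs no extra children, data or visits, and slightly reduces the analysis work.

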**Methods/design:**

The rationale and design of a randomized controlled trial examining the effects of a stationary cycling intervention for children with CP are outlined here. Sixty children with spastic diplegic CP between the ages of 7 and 18 years and Gross Motor Function Classification System (GMFCS) levels of I, II, or III will be recruited for this study. Participants will be randomly assigned to either an intervention (cycling) or a control (no cycling) group. The cycling intervention will be divided into strengthening and cardiorespiratory endurance exercise phases. During the strengthening phase, the resistance to lower extremity cycling will be progressively increased using a uniquely designed limb-loaded mechanism. The cardiorespiratory endurance phase will focus on increasing the intensity and duration of cycling. Children will be encouraged to exercise within a target heart rate (HR) range (70 – 80% maximum HR). Thirty sessions will take place over a 10–12 week period. All children will be evaluated before (baseline) and after (follow-up) the intervention period. Primary outcome measures are: knee joint extensor and flexor moments, or torque; the Gross Motor Function Measure (GMFM); the 600 Yard Walk-Run test and the Thirty-Second Walk test (30 sec WT).

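### The primary comparison uses change scores, and the planned ANCOVA adjusts for the stratification factors but not for the outcome's baseline value, which gives up precision

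*Protocol article*

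**What the plan says.** The Data analyses section of the protocol article describes two layers of analysis for the primary outcomes.

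- First, for the primary hypotheses: "Student t-tests (if normally distributed) or Wilcoxon rank sum tests (if non-normal) will be used to contrast the change from baseline within and between" the two groups. The response is change, and the test is unadjusted.
- Second, for the primary outcome measures: "Analysis of covariance procedures will be used to contrast changes adjusting for selective voluntary motor control (good versus fair) and age group". The response is again change.

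The two covariates are the factors used at randomization. Methods/design states: "There are two stratifying variables; age (younger, 7–11 and older, 12–18 years) and selective voluntary motor control ability (good versus fair"), and then: "Randomization to the intervention or control group will be blocked by these two variables". The baseline value of the outcome is not named as a covariate in either layer, although the abstract says: "All children will be evaluated before (baseline) and after (follow-up) the intervention period".

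The Sample size section plans on the unadjusted test: "A sample size of 30 in each group will have 80% power to detect a moderate effect size of 0.7", with a two-group t-test at two-sided 0.05 and 10% attrition taken into account.

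**The concern.** When an outcome is measured before and after treatment, subtracting the baseline is equivalent to fixing its regression coefficient at 1. Unless the true slope of follow-up on baseline is 1, this leaves baseline variation in the response as noise. It also leaves the estimate open to whatever baseline difference chance produces between two small arms. Estimating the slope removes both, and the data for it are already collected.

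This is not a detail left to an analysis plan that we cannot see. The article itself fixes the response and lists the covariates, and the list covers the strata only. At stake is power in a trial with few children to spare, and how far a single realised estimate can be moved by baseline imbalance.

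**Working it through.** **Inputs from the article (Sample size).** 30 per group, standardized effect 0.7, two-sided 0.05, two-group t-test, 10% attrition. 30 × 0.9 = 27 evaluable per group.

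**Assumptions, because the article is silent.** The correlation ρ between baseline and follow-up is set at 0.5, 0.7, 0.8 and 0.9. SDs are equal at the two visits. The effect of 0.7 is in SD units of change.

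**Step 1: the article's own figure.** With noncentrality δ = d√(n/2) and 2n − 2 degrees of freedom:

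- n = 30: δ = 0.7 × √15 = 2.71, power 76.0%
- n = 27: δ = 0.7 × √13.5 = 2.57, power 71.4%

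The stated 80% is not reproduced at either size. That is a separate sample-size matter; here 71.4% and 76.0% serve only as the reference for the unadjusted test.

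**Step 2: variance with and without baseline.** Let the outcome SD be s.

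- Change: 2s²(1 − ρ)
- Residual after adjusting for baseline: s²(1 − ρ²)
- Ratio: (1 + ρ)/2

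**Step 3: power with baseline adjustment.** The effect becomes 0.7/√((1 + ρ)/2), with 2n − 3 degrees of freedom.

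| ρ | Variance ratio | Adjusted effect | Power, 27 per arm | Gain over 71.4% (points) | Power, 30 per arm |
|---|---|---|---|---|---|
| 0.5 | 0.75 | 0.808 | 83.0% | 11.6 | 86.8% |
| 0.7 | 0.85 | 0.759 | 78.1% | 6.8 | 82.4% |
| 0.8 | 0.90 | 0.738 | 75.8% | 4.4 | 80.2% |
| 0.9 | 0.95 | 0.718 | 73.5% | 2.2 | 78.1% |

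Gains are taken from unrounded powers. Power reaches 80% at 27 per arm only if ρ is about 0.6 or lower (80.5% at 0.6), and at 30 per arm only if ρ is about 0.8 or lower.

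**Step 4: unequal SDs.** With SDs s₀ at baseline and s₁ at follow-up, Var(change) = s₀² + s₁² − 2ρs₀s₁ = s₁²(1 − ρ²) + (s₀ − ρs₁)². The last term is what the change score adds. It is never negative, so the direction does not depend on equal SDs, apart from the one degree of freedom. The size does.

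**Step 5: scale of the effect.** The article does not say which SD the 0.7 refers to. In SD units of follow-up, power at 27 per arm (change score, then baseline-adjusted) is 71.4% and 83.0% at ρ = 0.5, 90.3% and 94.2% at 0.7, and 97.9% and 98.8% at 0.8. On that reading the gain shrinks quickly as ρ rises.

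**Step 6: chance imbalance.** One standard error of the baseline difference at 27 per arm is √(2/27) = 0.27 SD. Given such a difference, the expected change contrast shifts by (1 − ρ) × 0.27 SD. The design effect on the same scale is 0.7√(2(1 − ρ)) SD.

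- ρ = 0.5: 0.136/0.700 = 19% of the design effect
- ρ = 0.7: 0.082/0.542 = 15%
- ρ = 0.9: 0.027/0.313 = 9%

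Stratification reduces this only as far as age group and motor control predict the baseline score.

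**The case against.** The strongest reply is that this is a matter of efficiency and not of error, and that its size rests on a correlation the article does not give. Both parts stand. Children aged 7 to 18 at GMFCS levels I to III differ widely, and over 10 to 12 weeks such spread tends to raise ρ, where the gain is smallest. The gains above are also measured against the unadjusted t-test. The gain over the planned strata-adjusted ANCOVA was not computed, and would be smaller if the strata already explain some of the variation in change that baseline would explain.

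A second reply concerns the remedy. Under Outcome data measurements, the 600-yard distance is capped, and the test ends at 15 minutes or after a stop of more than five seconds. A linear model is not clearly better than a rank method for such an outcome. This also stands, and the fix allows for it.

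A reader might infer more than the text supports:

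- *No test is decisive, and up to three compete.* The article ties the t-test or rank-sum test to the primary hypotheses and powers the trial on the t-test. Those two are alternatives under a rule, so at most two between-group tests apply per outcome. What remains is that the article does not say how to read a disagreement with the ANCOVA.
- *The normality switch inflates the type I error.* In a simulation of 8,000 trials per distribution, with 27 per arm and Shapiro-Wilk in each arm, the two-stage rule gave about 0.048 for normal, lognormal and t₃ data. Reporting the more favourable test would give 0.055 to 0.066, but the article does not allow that.
- *Regression to the mean biases the comparison.* Under randomization it acts equally on both arms in expectation.
- *The stratification is ignored.* The t-test leaves it out, but the planned ANCOVA adjusts for exactly those two factors.

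**Conclusion.** The point holds as one of lost precision and exposure to chance baseline imbalance, not of invalidity. Leaving out baseline is a choice the article states. With 27 per arm, 0.7 SD of change and equal SDs, adjustment raises power by about 12 points at ρ = 0.5 and about 2 at ρ = 0.9. No single figure should be quoted, because ρ is an assumption throughout.

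It would also be too much to infer that adjustment repairs the shortfall against the stated 80% power. At 27 per arm it does so only if ρ is about 0.6 or lower. The change is worth making because it costs almost nothing.

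**What to change.** Amend the Data analyses text as follows.

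1. Add the baseline value of the outcome to the ANCOVA already planned: follow-up (or change) on group, baseline value, age group and selective motor control. With baseline in the model, the two responses give the same group estimate.
2. Name this model the primary between-group analysis for each continuous primary outcome.
3. Keep the t-test and Wilcoxon test on change as pre-named sensitivity analyses.
4. For bounded outcomes such as the 600-yard distance, name a baseline-adjusted rank method (rank ANCOVA) in advance instead of choosing by a normality check.

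The cost is a few sentences and one degree of freedom, with no new data or visits. The downside is that little is gained if the pre-post correlation is near 0.9.
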